**Fig. 1 Fig1:**
[figure not shown]
Flow diagram participant timeline. SH = Schleswig-Holstein, federal state in northern Germany; PCPs = primary care physicians; h = hours; EbMG = Evidence-based Medicine – Guidelines; *t*
_0_ = baseline, pre-intervention time period; *t*
_1_ = post-intervention time period; *n* = number of cases

### Sample size

#### Primary outcome: evaluation of antibiotic prescribing rate in intervention groups compared to control group

Previous research has established that communication training can lead to a reduction of 12 % (95 % confidence interval −18.9 to −4.0) in antibiotic prescribing [17], with a mean of −4 % (standard deviation (SD) 15.6) in the intervention group and +8 % (SD 19.2) in the control group, respectively, from *t*_0_ to *t*_1_.

Additional definitions for sample size calculations are a power of 80 % and *α* = 5 %. A *t* test for unequal group sizes (Satterthwaite’s *t* test) results in 28 PCPs per study arm. Including an estimated dropout of 10 %, the total is 93 participants, yielding 31 per study arm.

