## Methods/Design

### Trial design

The trial is designed as a randomised, controlled trial postulating superiority of the interventions over conventional care in family practices. The study consists of three arms and a primary endpoint of antibiotic prescribing rates of PCPs for acute bronchitis, sinusitis and pharyngitis over a 3-month period starting around 1 month after the communication training and education in the usage of EbMG. Randomisation of either of the two intervention groups or the control group will be performed at practice level with a 1:1:1 allocation. Therefore, random permuted blocks will be generated. Due to the data format, practices with more than one physician represent one case. The person assigning the participants to the groups will do so blinded. Further blinding does not fit the trial design.

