### Outcomes

#### Primary outcome measures

Evaluation of the antibiotic prescribing rate in both intervention groups compared to the control group between baseline (meaning the prescribing rate of the three periods April–June 2013, 2014, and 2015) and post-intervention (April–June 2016)

To determine the antibiotic prescribing rate for each PCP, all patients with the target-diagnoses of acute bronchitis, sinusitis and pharyngitis (classified by the *International Classification of Diseases*, *version 10* (ICD-10) codes: J01.-; J02.-; J20.- [26]) are identified in the routine data of KVSH and the proportion of these patients who receive antibiotic prescriptions is calculated. The three diagnoses and corresponding antibiotic prescriptions are condensed into one rate for each PCP (in %). This will be completed for two time periods (*t*_0_ = baseline, before intervention: mean of quarter II in the years 2013–2015; *t*_1_ = post-intervention: quarter II in the year 2016). For each PCP the change from *t*_0_ to *t*_1_ will be calculated (rate *t*_1_-rate *t*_0_). For each study group, the mean of the antibiotic prescribing rates of all PCPs in the group (at *t*_0_ and *t*_1_) will be calculated. For our primary endpoint the two intervention groups will be regarded as one group which is compared to group C.

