### Recruitment of participants

All PCPs who have been members of the KVSH for at least the last five preceding years and who have made diagnoses of the defined ones are contacted via mail (*n* = 977). Furthermore, the information about the study and the invitation are spread through different channels: the Hausaerzteverband SH, which is a federal division of the biggest association of PCPs in Germany, further regional associations (Aerztenetze) as well as in the group of medical student trainers at the University of Luebeck.

Besides information on the study and the informed consent form, the invitation letter highlights the incentives for participants: credit points for continuing medical education as well as book vouchers. If more eligible PCPs apply for participation than needed, the first 93 are included and a waiting list is created.

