### Analysis

#### Statistical methods concerning study outcomes

##### Primary outcome

All randomised PCPs will be included and analysed as randomised. The combined intervention groups’ rate (group A + B) will be compared to the control group (C) with a *t* test for the group mean (= proportion of antibiotic prescribing). As an effect size the difference of differences or difference of change [16], respectively, is chosen. This depicts the difference from *t*_0_ to *t*_1_ between the intervention and control groups.

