### Strengths and limitations of the study

The randomisation will ensure a random distribution of characteristics and probably create nearly equal groups. Due to the number of participants, a prior stratification would not be reasonable. A limitation of the study is that randomisation must be carried out at practice level because the routine data cannot be assigned to the individual PCP in group practices. Therefore, untrained PCPs in group practices might bias the effect of the intervention.

Using the PCPs’ routine data instead of self-documentation bears the advantage that the data is not subject to selection bias: for example, if a PCP does not include all cases with the defined diagnoses in their documentation or if patients deny being in the study. Also, recall bias or effects due to the interviewer can be excluded. The Hawthorne effect is probably smaller, too, as the PCPs’ attention is not constantly drawn to patients with the relevant diagnoses. The routine data further allows the possibility of including several years as *t*_*0*_, which can balance extremes due to different seasonal variations. Extremes in *t*_1_ cannot be balanced, but a rise in antibiotic prescriptions due to a growth in infections in this time period would equally affect intervention and control groups.

Routine data is, at the same time, secondary data with known limitations: an often poorer data quality caused, for example, by misclassifications goes along with no possibility of external validation (e.g. of diagnoses) in our subsample. Further weaknesses are the lack of information on prescriptions that were not redeemed and using data covering only those patients who have statutory health insurance. Due to the data format, we do not have any further information about the ongoing of a patient’s disease, e.g. whether patients who did not use antibiotics suffer from complications afterwards. Information about side effects of antibiotics is also not available. However, these important issues will be part of the process evaluation.

Sample size calculation for this study was difficult because not only the effect size but also the *t*_0_ prescribing rate of antibiotics for the three diagnoses in Germany are based on estimates. Additionally, as in many trials, we will also be confronted with the self-selection bias of PCPs. Those interested or already sensitised for the issues (antibiotic prescription, communication skills) are more likely to participate in our study.

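### Randomisation and data are by practice, but the outcome rate, sample size, cap and analysis set are stated per physician, so the 80% power holds only if the 93 are 93 practices

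*Protocol article*

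**What the plan says.** All references are to the protocol article.

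**Stated by practice**
- Trial design places the 1:1:1 randomisation at practice level and adds: "Due to the data format, practices with more than one physician represent one case".
- Strengths and limitations of the study gives the reason: "randomisation must be carried out at practice level because the routine data cannot be assigned to the individual PCP in group practices".

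**Stated by PCP**
- Primary outcome measures: the three diagnoses and their prescriptions "are condensed into one rate for each PCP", and a change score is then formed for each PCP.
- Sample size: 28 PCPs per arm; with 10% dropout, "the total is 93 participants, yielding 31 per study arm".
- Recruitment of participants: if more eligible PCPs apply than are needed, "the first 93 are included and a waiting list is created".
- Analysis, Primary outcome: "All randomised PCPs will be included and analysed as randomised".

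**Who may take part**
- The PCPs subsection of the eligibility criteria admits group practices, provided that every PCP in them consents.
- The list of covariates for the MAAS-Global-D regression includes single versus shared practice, so group practices are expected.

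**The concern.** The two sets of statements agree only where each practice has one PCP, or where one PCP per practice is counted. In a group practice the per-PCP rate cannot be computed from the data described. Nothing says whether the cap falls at the 93rd physician or the 93rd practice, or how many physicians of one practice may count towards it.

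Two things are at stake for the primary comparison:

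- If several PCPs of one practice count towards the 93 and practices are analysed, there are fewer independent rates than the sample size calculation assumes.
- If PCPs are analysed as the outcome and analysis sections are worded, colleagues in one practice carry the same rate. A t test that treats them as independent understates the standard error.

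The exploratory MAAS-Global-D regression meets the same difficulty: an individual's score is paired with a rate that, in a shared practice, belongs to the whole practice.

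**Working it through.** **Inputs from the Sample size section.** Mean change −4 (SD 15.6) in the intervention group and +8 (SD 19.2) in the control group, so a difference of 12 points; "a power of 80 % and *α* = 5"%; Satterthwaite t test with unequal groups; 10% dropout. The comparison is A + B versus C, so the groups are 2n and n. The section does not say whether alpha is one- or two-sided; two-sided reproduces its figure.

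**Step 1: reproduce the plan's figure.**

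SE = √(15.6²/(2n) + 19.2²/n), and power comes from the noncentral t distribution with Satterthwaite degrees of freedom.

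- n = 28: SE = √(243.36/56 + 368.64/28) = √(4.346 + 13.166) = 4.185. Noncentrality = 12/4.185 = 2.87 on about 45 degrees of freedom. Power is 80.1%.
- n = 27: power is 78.6%, so 28 is the smallest n that reaches 80%.
- Dropout: 28 × 1.10 = 30.8, rounded up to 31 per arm, 93 in total.
- After the planned dropout: 93 × 0.9 = 83.7 units, 27.9 per arm. Power is 80.0%, so there is no reserve.

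**Step 2: practices as the unit, cap at 93 PCPs.** Let m be the mean number of counted PCPs per practice. The article does not give m, so a range is shown. The number of practices is 93/m; after dropout, n per arm = 0.9 × 93/(3m). The stated SDs are kept.

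| m (assumed) | Practices | n per arm after dropout | SE | Power |
|---|---|---|---|---|
| 1.0 | 93 | 27.9 | 4.19 | 80% |
| 1.1 | 84.5 | 25.4 | 4.40 | 76% |
| 1.25 | 74.4 | 22.3 | 4.69 | 70% |
| 1.5 | 62 | 18.6 | 5.13 | 62% |

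To have 93 practices at m = 1.1, 1.25 and 1.5, about 103, 117 and 140 PCPs would be needed (93 × m, rounded up).

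**Step 3: if practice rates vary less than the stated SDs.** Suppose the SDs describe single physicians and the rate of a practice is an average over its physicians. The loss then follows the design effect 1 + (m − 1) × ICC applied to 56 versus 28. The ICC is not given either.

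- m = 1.25: ICC 0.1 gives a design effect of 1.025 and power of 79%; ICC 0.3 gives 1.075 and 77%.
- m = 1.5: ICC 0.1 gives 1.05 and 78%; ICC 0.3 gives 1.15 and 74%.

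The loss is smaller, but power is still under 80%.

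**Step 4: if a shared rate is entered once per PCP.** Identical rates within a practice give a variance inflation of Σm²/Σm. For illustration, take 93 PCPs from 47 single-handed practices and 23 pairs (70 practices): (47 + 23 × 4)/93 = 139/93 = 1.495. The actual size of a nominal 5% test is then about 2 × [1 − Φ(1.96/√1.495)] = 10.9%. The split is assumed; the direction does not depend on it.

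**The case against.** The strongest reply is that the unit is already fixed. Trial design says a group practice is one case, and only practices are randomised, so the randomised PCPs of the analysis section can be read as randomised practices. There are also signs that one PCP per practice was meant. The eligibility section lists PCPs and their colleagues separately for consent. The reason given for colleagues' consent is that a trained PCP will influence them. The limitations mention untrained PCPs in group practices. On that reading 93 participants are 93 practices, and the power is as stated.

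This reply stands as a possible reading, and it rules out a flat claim. A reader might infer that stopping at 93 PCPs fails to deliver 80% power. The document does not support that, because consenting is not shown to mean being counted. But it does not establish the benign reading either: no rule limits a practice to one counted PCP, and the cap is worded for PCPs.

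A reader might also infer that type I error is inflated under the plan. That too goes further than the text. The one-case rule argues against entering a practice's rate more than once; the per-PCP wording of the outcome and analysis sections merely leaves it possible.

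Finally, a reader might add a loss from untrained colleagues who dilute the practice rate. The two losses cannot both apply to the same colleagues: those counted in the 93 would, in the intervention arms, be trained, and those who dilute the effect are not. Dilution is already disclosed as a limitation, the protocol expects some spill-over to colleagues, and its size cannot be derived from the document. It is a separate matter.

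**Conclusion.** The contradiction over the unit is real and affects the primary analysis. The arithmetic behind 28, 31 and 93 is reproduced; what is unsettled is the unit that those numbers count. The stated power is conditional on 93 separate practices. Once the planned dropout occurs, any mean above one counted PCP per practice takes power below 80%, provided that rates within a practice are positively correlated.

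Over the assumed range of 1.1 to 1.5 counted PCPs per practice, power is 76% down to 62% with the stated SDs. With an ICC of 0.1 to 0.3 it is 78% to 74% at 1.5. Practice size, the ICC and the unit behind the cited SDs are not in the document, so these figures illustrate the exposure and do not estimate it. The type I error figure of about 11% applies only if a practice's rate is entered once per physician.

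**What to change.** State in Primary outcome measures, Sample size, Recruitment of participants and the primary analysis paragraph that the practice is the unit of outcome, sample size, cap and analysis. Each practice then has one rate, and the cap applies at the 93rd practice, 31 per arm. If recruitment stops at 93 PCPs from fewer practices, restate the power for the practices actually randomised.

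For the exploratory MAAS-Global-D regression, use one record per practice with the mean score of its recorded PCPs, or restrict the analysis to single-handed practices.

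The cost is wording and, if needed, one restated power figure; no new data are required. Trial status says recruitment is under way, so the meaning of the cap can still be settled. If the 93 PCPs applying come from fewer than 93 practices, a cap counted in practices means enrolling further practices, which the waiting list could supply.

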### Recruitment of participants

All PCPs who have been members of the KVSH for at least the last five preceding years and who have made diagnoses of the defined ones are contacted via mail (*n* = 977). Furthermore, the information about the study and the invitation are spread through different channels: the Hausaerzteverband SH, which is a federal division of the biggest association of PCPs in Germany, further regional associations (Aerztenetze) as well as in the group of medical student trainers at the University of Luebeck.

Besides information on the study and the informed consent form, the invitation letter highlights the incentives for participants: credit points for continuing medical education as well as book vouchers. If more eligible PCPs apply for participation than needed, the first 93 are included and a waiting list is created.

### Data collection and management

#### Diagnoses and antibiotic prescribing

KVSH provides data about diagnoses to ZI over an intermediate body. ZI also has data on redeemed antibiotic prescriptions. Diagnoses and prescriptions are not originally linked but data sources are joined by ZI and provided as a joined data stream to KVSH. This routine data by KVSH forms the basis of a shortened dataset for the study team. Individual patients cannot be identified in the data set due to anonymisation.

#### Communication skills

During *t*_1_, PCPs in the intervention groups record six videos of consultations in their practice. The PCPs choose the videos themselves (preferably ones in which the PCP recognises their own usual behaviour) and send them via a secure USB stick to the study centre. The videos are then rated by researchers using the MAAS-Global-D rating scale. The English version of the instrument has been tested for reliability with Cronbach’s *α* and showed values of 0.78 - 0.86 [27, 28]. Furthermore, a comparison of the rating scale and the Common Ground instrument showed an acceptable value (0.59), which is an indicator for convergent validity [28].

### Data quality

A short questionnaire about the PCPs’ socio-demographics, the results of the MAAS-Global-D rating and the data from the process evaluation will be entered locally at the study centre. Where applicable, values can be chosen from a list of codes and their meaning is captured in a codebook. To secure and promote data quality, all data will be checked for double data entry and plausibility of range of values before analysis. Potential changes to the dataset are documented in a separate file.

### Analysis

#### Statistical methods concerning study outcomes

##### Primary outcome

All randomised PCPs will be included and analysed as randomised. The combined intervention groups’ rate (group A + B) will be compared to the control group (C) with a *t* test for the group mean (= proportion of antibiotic prescribing). As an effect size the difference of differences or difference of change [16], respectively, is chosen. This depicts the difference from *t*_0_ to *t*_1_ between the intervention and control groups.

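### The primary t test is worded on the prescribing rate, while the effect size and the sample size are on the change from baseline; one analysis, preferably baseline-adjusted, should be named

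*Protocol article*

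**What the plan says.** All references are to the Protocol article.

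- **Analysis, Primary outcome.** The combined intervention groups' rate is compared with control by a t "test for the group mean (= proportion of antibiotic prescribing"). The next sentence reads "As an effect size the difference of differences or difference of change". No covariate is named, nor is the version of the t test.
- **Trial design.** The trial has "a primary endpoint of antibiotic prescribing rates of PCPs for acute bronchitis, sinusitis and pharyngitis over a 3-month period", starting about one month after training. This describes the post-intervention rate.
- **Outcomes, Primary outcome measures.** Baseline t0 is the mean of quarter II in 2013, 2014 and 2015; t1 is quarter II of 2016. "For each PCP the change from" t0 to t1 is then calculated, as the t1 rate minus the t0 rate.
- **Sample size.** The planning values are changes: "with a mean of −4 % (standard deviation (SD) 15.6) in the intervention group and +8 % (SD 19.2) in the control group". The calculation uses "a power of 80 % and *α* = 5" % and a t "test for unequal group sizes", named there as Satterthwaite's.
- **Secondary outcomes measures.** The t0 rate is an independent variable only in the secondary regression on the communication score.
- **Strengths and limitations of the study.** Randomisation is not stratified.

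**The concern.** The article states the primary test, so this is not a detail left to an analysis plan, and it states the tested quantity in two ways. The p-value could come from the t1 rate while the reported effect is a difference of changes, and the two can disagree. A choice between two primary analyses also stays open until the data are seen.

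The trial is sized to just reach 80% power on the change scale. A test on another scale does not inherit that power. The t0 rate is computed for every practice, yet the primary analysis either subtracts it with a fixed coefficient of 1 or, read literally, leaves it out.

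**Working it through.** **1. Reproducing the plan's figure.** Inputs from the sample size section: difference −4 − 8 = −12 points, SDs of change 15.6 and 19.2, power 80%, α 5%. Sidedness is not stated; two-sided is assumed. Allocation 1:1:1 with A+B pooled gives 2:1.

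- Variance of the difference at 56 versus 28: 15.6²/56 + 19.2²/28 = 4.346 + 13.166 = 17.51.
- Noncentrality: 12/√17.51 = 2.868. Satterthwaite df 45.3, critical value 2.014.
- Power: 80.1%. At 54 versus 27 it is 78.6%, so 28 is the smallest arm size that reaches 80%.
- Dropout: 28 × 1.1 = 30.8, so 31 per arm and 93 in total, as stated.

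The stated 28 is thus the size for a Satterthwaite test on **change**. (A one-sided 1:1 calculation also gives 28, but it does not fit the stated unequal group sizes.)

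**2. Model for the other analyses.** The protocol gives no correlation, so assume that all quarters have the same variance (set to 1) and the same pairwise correlation ρ. With t0 as a three-quarter mean, as planned:

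- var(t0) = (1 + 2ρ)/3 and cov(t0, t1) = ρ
- var(change) = 1 + (1 + 2ρ)/3 − 2ρ = 4(1 − ρ)/3
- residual variance of t1 after adjusting for t0 = 1 − 3ρ²/(1 + 2ρ)
- slope of t1 on t0 = 3ρ/(1 + 2ρ)

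The SDs of change are held at 15.6 and 19.2, and the variances of the other two analyses are scaled from them. Under randomisation the expected difference is 12 points on all three scales.

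**3. Results at 56 versus 28.**

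| ρ | Slope | Var(t1 only)/var(change) | Power, t1 rate only | Var(adjusted)/var(change) | Power, adjusted for t0 |
|---|---|---|---|---|---|
| 0.3 | 0.56 | 1.07 | 77% | 0.891 | 84.5% |
| 0.5 | 0.75 | 1.50 | 63% | 0.938 | 82.6% |
| 0.7 | 0.875 | 2.50 | 43% | 0.969 | 81.4% |
| 0.9 | 0.96 | 7.50 | 18% | 0.991 | 80.5% |

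Example at ρ = 0.5: var(change) = 0.667 and adjusted variance = 1 − 0.75/2 = 0.625, so the ratio is 0.625/0.667 = 0.938. The ratio for t1 only is 1/0.667 = 1.50. The t1-only test is weaker than the change test whenever 4(1 − ρ)/3 < 1, that is, for ρ above 0.25.

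**4. Chance imbalance.** At ρ = 0.5 the change score subtracts the whole baseline imbalance where 0.75 of it is warranted. An illustrative chance imbalance of 4 points would leave (1 − 0.75) × 4 = 1 point in the estimate. Adjustment estimates the slope instead of fixing it.

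**5. Version of the t test.** Take 62 versus 31 with SDs 15.6 and 19.2.

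- True variance: 243.36/62 + 368.64/31 = 15.82.
- A pooled test would expect (61 × 243.36 + 30 × 368.64)/91 × (1/62 + 1/31) = 284.7 × 0.0484 = 13.77, which is too small.
- Simulated size of the pooled test: about 6.7% (0.0665 in 200,000 trials; a repeat with 400,000 gave 0.0662). Welch: 4.9%.

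**The case against.** The strongest reply is that the change is plainly what is meant. The abstract describes rates before and after the intervention, the outcome section computes the change, the secondary outcomes refer back to the mean of change, and both the sample size and the effect measure are on change. The trial design sentence may only be fixing the post-intervention window. Most of this stands: the change is the likelier reading, so the powers for the t1-only test show what the loose wording would permit, not what the trial can be expected to have. The sentence that defines the test still names the rate and needs correcting.

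Four stronger inferences are tempting, and the documents do not support them.

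- **That the change-score test is biased or the sample size wrong.** Under randomisation the test is valid, and it is the one that the 28 per arm fits.
- **That adjustment would lift power to about 90% or 86%** (ρ of 0.5 or 0.7). Those figures need equal SDs at t0 and t1. The plan averages three quarters for t0, which moves the best slope towards 1 and makes the change score nearly efficient.
- **That the type I error is inflated.** No section names a pooled test; the only version named is Satterthwaite's. The 6.7% applies only if a pooled test were run.
- **That the baseline significance tests under Additional analyses decide on adjustment.** That section does not link them to it.

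It can also be said that covariate adjustment is often left to an analysis plan. That is fair for the choice of covariates, but not for a conflict over which quantity the primary test uses.

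**Conclusion.** The concern holds as an inconsistency in the primary analysis, together with a small avoidable loss of precision. The test is worded on the rate; the effect measure, the outcome computation and the sample size are on the change, and the planned 80% power belongs to a Satterthwaite test on change. A literal test of the t1 rate would have about 63%, 43% or 18% power at ρ of 0.5, 0.7 or 0.9.

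If the change is tested, the analysis is valid. Adjustment for t0 would then save 1 to 11% of variance for ρ from 0.9 down to 0.3, and would deal better with chance imbalance in an unstratified trial. These figures rest on the planned SDs of change, equally correlated quarters of equal variance, and an assumed ρ. The ambiguity matters more than the efficiency.

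**What to change.** State one primary analysis: a linear regression of the practice t1 rate on group (A+B versus C) with the practice t0 rate as covariate, heteroscedasticity-robust standard errors, and the adjusted difference with its 95% confidence interval. With t0 in the model, the group coefficient is the same whether t1 or the change is the outcome, so the question of rate or change falls away.

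Keep the unadjusted difference in change as a sensitivity analysis, and name its test in the analysis section as the Satterthwaite (Welch) version. Align the trial design, primary outcome measures and analysis sections so that they describe the same quantity.

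The cost is wording only. No new data are needed because t0 is already computed, and 28 per arm before dropout can stay as a slightly conservative figure. The change should be made before t1 data are seen.
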